### Primary outcomes

The primary outcome for Aim 1 is the feasibility of tSCS in subacute SCI. Safety will be evaluated by cardiovascular responses before, during, and after single and repeated tSCS sessions, including changes in systolic and diastolic BP and heart rate, as well as the occurrence and severity of cardiovascular adverse events related to tSCS or study procedures.

The primary outcome for Aim 2 is the feasibility of recurrent tSCS during the inpatient rehabilitation phase (Project A), defined by (1) adherence to the stimulation and assessment protocols, (2) recruitment and retention rates throughout the study period, and (3) the frequency and severity of adverse events related to tSCS or study procedures. These feasibility indicators align with established guidelines for pilot and feasibility trials [81]. In addition, between-group differences in preliminary autonomic and cardiovascular outcomes will be explored following completion of the five-session inpatient phase (Project A). These outcomes include physiological and clinical measures of autonomic and cardiovascular function, such as systolic BP responses during the sit-up test, the frequency and severity of autonomic dysreflexia and orthostatic hypotension during 24-hour BP monitoring, and patient-reported symptoms of autonomic dysfunction assessed using the ADFSCI.

The primary outcome for Aim 3 is the change in systolic BP during orthostatic stress, assessed using the sit-up test or head-up tilt test, measured at baseline, following completion of the intervention, and at six-month follow-up.

### Statistical analysis

This is a two-phase clinical trial consisting of a pilot RCT (Project A) followed by a single arm pre- and post-experimental trial (Project B). A total of 26 participants with subacute (<six months since injury) cervical or upper thoracic ≥T6 AIS A–C SCI will be enrolled (Sham group n = 13, tSCS group n = 13). Descriptive statistics will be generated for the primary outcomes, feasibility outcomes, as well as demographic a clinical characteristic. Between group comparisons at baseline will be conducted using independent sample t-tests, Chi-square analyses, and Mann Whitney U tests as appropriate. Statistical analysis will be performed using R version 4.1.2 and the R studio program. This study is designed as a pilot trial, and analyses will primarily focus on feasibility, safety, and exploratory trends. Results will be interpreted in accordance with the CONSORT extension for pilot and feasibility trials

For Aim 1, we will evaluate the feasibility of tSCS by comparing cardiovascular responses before, during and after single and repeated tSCS sessions. Changes in systolic and diastolic BP and heart rate will be analysed using linear mixed models for repeated measures, with time (session) as a within-subject factor. Additionally, feasibility outcomes, including adherence rate, recruitment rate, and the frequency of adverse events, will be summarized descriptively.

For Aim 2, we will use Between-participant analyses assessing group differences in feasibility and preliminary autonomic outcomes between the Sham and tSCS groups after completion of the five-session inpatient phase (Project A). Linear mixed models will be used to assess the effects of time and intervention group, with baseline values included as covariates.

For Aim 3, within-participant analyses will examine longitudinal changes following the 18-session outpatient continuation phase (Project B) and at six-month follow-up. Descriptive statistics and standardized effect sizes (Cohen’s d) will be reported to estimate the magnitude of changes.

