### Transcutaneous Spinal Cord Stimulation (tSCS)

A portable tSCS device (SCONE and TESCoN, SpineX Inc., USA, ARC-EX, ONWARD Medical, Netherland) will be used to deliver biphasic 1ms pulses with 10kHz carrier frequency at 30 Hz. The device will be selected based on availability. This stimulation paradigm has demonstrated autonomic recovery in our previous studies [41,42,45]. The location of tSCS is predetermined at T11-T12 and L1-L2 vertebral levels. The stimulation intensity will range from 10 to 230 mA, and selecting the optimal therapeutic stimulation parameters will involve the following criteria: 1) a strong but comfortable sensory experience (initial slight tingling at the site of the electrode followed by some pressure or paraesthesia in skeletal muscles), described as a 5–7 on a 10 point Likert scale, 2) a stable systolic BP not more than 20 mmHg above baseline, and 3) without any symptoms of autonomic dysreflexia (i.e., sweating, goosebumps, tunnel vision, headache, etc.). The stimulation will be reduced if any of the above criteria is not satisfied as well if there are visually detectable skeletal muscle contractions. We will use two self-adhesive round electrodes (diameter of 2.0 cm) placed on the skin between spinous processes at the midline over the vertebral column as a cathode, and two rectangular 7.5  ×  12.5 cm self-adhesive electrodes located symmetrically on the skin over the iliac crests as anodes. The tSCS stimulator will be set with an open-loop stimulation using the same intensity throughout the session.

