### Assessments

**Cardiovascular Monitoring.** Cardiovascular adverse events associated with tSCS at rest will be recorded. We will document the frequency and severity of abnormal BP responses, as well as cardiac responses including tachycardia, bradycardia, arrhythmia, and any associated symptoms. Twenty four-hour BP monitoring will also be used to track BP at day and night [65,66]. Participants will maintain a diary documenting daily activities such as sleep and wake, bowel and bladder management, taking medications, eating, and any instances of symptoms of autonomic dysreflexia and hypotension [67]. The monitoring involves wearing a compact digital BP device (Meditech Ltd., Budapest, Hungary), which is connected to a cuff around the upper arm. The device automatically measures BP at regular intervals, typically every 15 minutes during the day and 60 minutes at night. Heart rate variability will also be assessed. Time-domain and frequency-domain analyses will be performed to evaluate sympathetic and cardiac parasympathetic activity [68], in accordance with the European task force heart rate variability guidelines and based on our prior work [69]. Participants will fill out the Autonomic Dysfunction Following Spinal Cord Injury (ADFSCI) questionnaire at each assessment phase [70]. The ADFSCI questionnaire has participants self-report on the frequency and severity of autonomic dysreflexia episodes.

**Continuous Hemodynamic Monitoring During Orthostatic Challenge**. All participants will undergo continuous beat-by-beat BP monitoring and electrocardiography during a sit-up or head-up tilt test performed with and without tSCS to evaluate cardiovascular safety and real-time autonomic responses [71–73]. Orthostatic blood pressure responses are evaluated during transition from a supine to an upright position of at least 60 degrees [74].

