### Data management and safety

All data collected (electronic or hardcopy documents) will be coded with unique identification numbers and stored centrally on the database, a password-protected computer, or in a locked filing cabinet in a secure laboratory space only accessible to the study investigators. To ensure information quality and accuracy after publication, all data will be stored for 6 years, and then subsequently destroyed.

Any adverse events reported during the intervention will be documented with information pertaining to their severity and anatomical location. The study coordinator will immediately report adverse events to the ethics board and Data and Safety Monitoring Committee (DSMC), which is comprised of three external, independent physician scientists with no involvement in the study, as well as the appropriate ethics board. The DSMC is responsible for safeguarding the interests of trial participants, assessing the safety and effect of the interventions during the trial, and monitoring the overall conduct of the clinical trial. The DSMC also provides recommendations for continuing or discontinuing the trial and outcome data use for participants who discontinue the trial. The trial progress will be biannually reported to the DSMC.

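### The Aim 1 model of BP and heart rate around sessions has no group term and no before/during/after term, so the randomised sham arm is not used; the adverse event wording is also inconsistent

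*Protocol article*

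**What the plan says.** **Model.** In the protocol article, Statistical analysis, Aim 1 is addressed by "comparing cardiovascular responses before, during and after single and repeated tSCS sessions". The changes in systolic BP, diastolic BP and heart rate "will be analysed using linear mixed models for repeated measures, with time (session) as a within-subject factor". No other factor is named. The next paragraph, on Aim 2, names both time and intervention group, with baseline as a covariate, and places the comparison after the five inpatient sessions.

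**Design.** Study design and setting describes Project A as a two-arm, sham-controlled pilot RCT meant to evaluate safety as well as efficacy, with 13 per arm.

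**Adverse events.** Under Primary outcomes, Aim 1 counts "the occurrence and severity of cardiovascular adverse events related to tSCS or study procedures" and Aim 2 counts "the frequency and severity of adverse events related to tSCS or study procedures". Assessments states: "Cardiovascular adverse events associated with tSCS at rest will be recorded". Two other places set no relatedness limit. In the Aim 1 analysis paragraph, "the frequency of adverse events, will be summarized descriptively", and in Data management and safety, "Any adverse events reported during the intervention will be documented with information pertaining to their severity and anatomical location".

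**Titration.** One criterion for choosing the intensity is "a stable systolic BP not more than 20 mmHg above baseline"; stimulation is reduced when a criterion is not met.

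**The concern.** The question put in Aim 1 and the model offered for it do not match in two respects.

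First, a session factor describes change from one session to the next. The question is how BP and heart rate move within a session, which needs a phase term (before, during, after).

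Second, nothing in the model separates tSCS from sham. The Background section describes cardiovascular instability that often persists beyond the acute phase, so some change without any stimulation effect is plausible. A randomised control exists to absorb that change, and the stated model does not call on it.

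For adverse events, a tally limited to related events rests on an attribution judgement in a population where hypotension and dysreflexia are expected anyway. A tally of all events by arm rests on randomisation. The protocol article supports both readings, so it is not settled which table will be the primary one. At stake is how well the trial can answer its lead safety question from data it already plans to collect.

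**Working it through.** **1. The plan's own figure.** Aim 1 has no stated number. The only BP variability given is in Sample size: 16.2 ± 12.6 mmHg, so d = 16.2/12.6 = 1.286 (stated as 1.29). A two-sided two-sample t-test at α = 0.05 with d = 1.29 has power 0.779 at 10 per group and 0.821 at 11, so the stated 11 reproduces as a per-group figure. The SD of 12.6 is borrowed below as an assumption. It comes from four people with epidural stimulation during head-up tilt, not from resting tSCS sessions.

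**2. What a session factor measures.** Suppose stimulation raises BP by 10 mmHg during every session and by nothing before or after (illustrative). With three phases, each session mean rises by 10/3 = 3.3 mmHg, equally in all five sessions. The differences between sessions are then 0, and a session-only model does not show the response.

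**3. What the missing group term does.** The text does not say which arms enter the model.

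- Both arms: a response of +10 in tSCS and 0 in sham averages to (13 × 10 + 13 × 0)/26 = +5 mmHg.
- tSCS arm only: any background change is read as a tSCS effect.

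**4. Size of the second problem.** Assume no tSCS effect, SD of within-person change 12.6 mmHg, n = 13, and a one-sample two-sided t-test. The standard error is 12.6/√13 = 3.49 mmHg.

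| Assumed drift (mmHg) | Noncentrality = drift/3.49 | P(p < 0.05), tSCS arm only | P(p < 0.05), tSCS vs sham |
|---|---|---|---|
| 5 | 1.43 | 0.26 | 0.05 |
| 8 | 2.29 | 0.56 | 0.05 |
| 10 | 2.86 | 0.75 | 0.05 |

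The drift values are assumptions; the documents give none.

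**5. Precision of the sham contrast.** The 95% half-width is t(0.975, 2n − 2) × SD × √(2/n).

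- 13 per arm: 2.064 × 12.6 × 0.392 = 10.2 mmHg, against 2.179 × 3.49 = 7.6 mmHg for the within-arm change.
- 11 per arm: 11.2 mmHg. 10 per arm (20% dropout leaves 13 × 0.8 = 10.4): 11.8 mmHg.
- The half-width is proportional to the SD, 10.2/12.6 = 0.81 × SD at 13 per arm. Half the SD (6.3) would give 5.1 mmHg.

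**6. Precision for events.** With an assumed background proportion p in both arms, the risk difference half-width is 1.96 × √(2p(1 − p)/13). This is 0.31 at p = 0.2, 0.35 at p = 0.3 and 0.38 at p = 0.5.

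**7. Does Aim 2 fill the gap?** Its between-arm outcomes are sit-up BP, dysreflexia and orthostatic hypotension on 24-hour monitoring, and the ADFSCI questionnaire, all after the inpatient phase. BP and heart rate around individual sessions appear under Aim 1 only. Aim 2's adverse event component is also limited to related events.

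**The case against.** The strongest reply is that an article's sentence is not a full model specification. Naming one within-subject factor does not exclude others, the sentence before it states the phase contrast, and a statistical analysis plan may hold the remaining terms. This has some force. But the group term is written out for Aim 2 one paragraph later, so its absence from Aim 1 reads as a choice. Nothing in the text would lead an analyst to include sham in Aim 1.

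A second reply is that a within-subject Aim 1 is legitimate in a pilot. Aim 1 concerns single sessions, all participants also have an orthostatic test with and without tSCS, and a before/during contrast removes slow drift between sessions. That stands in part. Drift within a session, for instance from rest or posture, remains, and the orthostatic test is not the resting session. The percentages in step 4 therefore apply to drift in the contrast actually tested, and its true size is unknown.

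A third reply is that pooling the arms is the less natural reading, because the text speaks of tSCS sessions. That is fair; the uncontrolled reading is the more likely one.

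On adverse events, a reader might infer that the trial counts only related events. The documents do not support that: the Aim 1 analysis paragraph and Data management and safety carry no such limit, and Assessments also plans to document abnormal BP and cardiac responses generally. A reader might also infer that sham events could never qualify, or that unblinded staff decide relatedness. The wording includes study procedures, which can capture sham events, and no section says who judges relatedness.

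**Conclusion.** The point holds for the acute cardiovascular response. The stated Aim 1 model contains neither the phase contrast it is meant to estimate nor the randomised comparison that the design provides, and Aim 2 does not supply it. With an SD of 12.6 mmHg and drift of 5 to 10 mmHg, both assumed, a one-arm analysis would signal an effect that is not there in 26% to 75% of trials. The sham contrast removes that error at the price of a half-width of about 10 mmHg rather than 7.6. No number stated in the protocol changes. With 13 per arm this is estimation, which suits a pilot.

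The adverse event passages are inconsistent with one another and must be reconciled.

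Two stronger conclusions do not follow. One is that background dysreflexia cannot be separated from a tSCS effect anywhere in the trial: Aim 2 compares dysreflexia and orthostatic hypotension on 24-hour monitoring between arms. The other is that the titration rule makes the result safe by construction: the limit concerns rises in systolic BP only, not falls, diastolic BP, heart rate or arrhythmia. It does mean that mean systolic change partly reflects the rule, so the mean alone is an incomplete summary.

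**What to change.** - **Model.** For Project A, fit phase (before/during/after), group and their interaction, plus session number, with participant random effects. Report the tSCS-minus-sham difference in during-minus-before systolic BP, diastolic BP and heart rate with 95% CIs, presented as estimates rather than tests.
- **Adverse events.** Align the wording of Primary outcomes, Assessments, Statistical analysis and Data management and safety. Tabulate all documented adverse events by arm, with related events as a secondary split.
- **Titration.** Describe by arm the sessions in which systolic BP exceeded the stated limit or intensity was reduced. Reductions will be informative mainly in the tSCS arm, since sham is ramped down and switched off in any case. The clinical rule itself stays as it is.

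The cost is a slightly larger model and table, and a wider interval than for the within-arm change. Most of the data are already planned, and the adverse event recording window need not be extended.

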## Discussion and limitations

While spinal cord stimulation research is accelerating, few studies have assessed the applications of tSCS for use in inpatient settings and using a RCT design. Furthermore, there are no studies that have yet tested the effect of tSCS on comprehensive cardiovascular function including orthostatic hypotension and autonomic dysreflexia as well as pelvic organ function in IRF up to six-month post-injury. Thus, we propose to conduct the first study investigating the feasibility of tSCS following acute SCI.

### Data management and safety

All data collected (electronic or hardcopy documents) will be coded with unique identification numbers and stored centrally on the database, a password-protected computer, or in a locked filing cabinet in a secure laboratory space only accessible to the study investigators. To ensure information quality and accuracy after publication, all data will be stored for 6 years, and then subsequently destroyed.

Any adverse events reported during the intervention will be documented with information pertaining to their severity and anatomical location. The study coordinator will immediately report adverse events to the ethics board and Data and Safety Monitoring Committee (DSMC), which is comprised of three external, independent physician scientists with no involvement in the study, as well as the appropriate ethics board. The DSMC is responsible for safeguarding the interests of trial participants, assessing the safety and effect of the interventions during the trial, and monitoring the overall conduct of the clinical trial. The DSMC also provides recommendations for continuing or discontinuing the trial and outcome data use for participants who discontinue the trial. The trial progress will be biannually reported to the DSMC.

### Ethics and dissemination

This pilot study will be conducted in accordance with the Declaration of Helsinki and is consistent with the International Conference on Harmonisation Good Clinical Practice Guidelines, as well as applicable regulatory requirements. The study protocol was initially approved by the University of Washington Institutional Review Board (UW IRB) (STUDY00020243). The UW IRB and DSMC will be contacted when the trial makes any important protocol modifications. The feedback base on functional outcome measure results can be provided to participants for their adherence and benefits. The results of this pilot trial will be presented at national and international conferences and will be published in peer-reviewed journals. All subsequent manuscripts will be reported in conjunction with the Consolidated Standards of Reporting Trials. Extensive, individualized feedback will be provided to each participant upon completing the trial.
